**Fig 1 pone.0272481.g001:**
[figure not shown]
Potential mechanisms and pathways through which Bolsa Familia Program (BFP) may affect mental health-related hospitalizations and suicide among children and youth.

Therefore, the main potential mechanisms this project will test, through which BFP may be associated with better mental health outcomes are: (i) by reducing parental mental illnesses and family separations; (ii) by improving school retention (BFP has conditionalities related to education and health); (iii) by reducing exposure to violence; and finally, (iv) by decreasing impulsivity (Fig 1).

This protocol offers a unique opportunity to test these mechanisms in a countrywide dataset, and allows subgroup analyses. Considering that the impact of those factors may happen differently among more vulnerable groups, such as black youth, women, youth with lower income and living in deprived areas, after examining the impact of cash transfers on interrupting the pathways between poverty and poor mental health through one or more mechanisms previously mentioned (e.g., improving educational outcomes, reducing impulsivity, etc). We will then evaluate the differential impact of BFP across race and gender, and how this might be explained by the mechanisms. If the effect of the cash transfer is stronger among minorities, decreasing inequalities, it can also be one of the mechanisms through which this program may improve youth mental health.

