Our data of over half of the Brazilian population will help understand both (observationally) the association of multiple factors on both mental illness and suicide, and the impact of interventions targeting some of these factors. Within each broad analysis, we will explore pathways, mechanisms and interactions/moderators. This is especially important in LMICs, such as Brazil, where implementing preventative measures may be more challenging as a result of cultural and socioeconomic factors, limited resources, as also in large continental countries because of size and distribution of the population [15]. This study’s aims are as follows:
To use large national datasets to evaluate the effect of a broad range of social drivers and of a social-economic intervention on youth mental health,To test four mechanisms and pathways (reducing parental mental illness; increasing school retention; reducing exposure to violence; decreasing impulsivity) of the social-economic intervention on reducing mental illness among youth,To evaluate whether equity is a moderator of the effectiveness of the cash transfer program, e.g., whether the Brazilian cash transfer program improves the lives of the most vulnerable subgroups (with lower income, black population, and women) compared to less vulnerable groups, thereby reducing mental health disparities, andInvestigate early life exposures, intergenerational aspects, and to forecast the impact of socioeconomic changes and cash transfers mitigation effects in Brazil until 2030 using microsimulation models, also modelling the impact of the current COVID-19 related economic recession.

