*Fourth*, the uniquely large number of individuals of our dataset provides sufficient statistical power to assess the effects and test mechanisms of BFP on a high number of subpopulations, in terms of demographic, geographic, social, and economic conditions, thereby taking advantage of Brazil’s extreme social inequalities. To date, knowledge about the potential of Cash Transfer Programs (CCTs) on mental illness and suicide has been limited to small trials where, in general, the CCT program was not part of a national poverty alleviation strategy, and evaluations have been focused on poor populations of a few lower-income countries. This study provides the exceptional occasion to assess potential effect modification disparities, evaluating whether the Brazilian cash transfer program improved the lives of most vulnerable subgroups (with lower income, black population, and women) compared to less vulnerable groups, therefore, reducing inequalities.

*Fifth*, this study contributes to translational science with the systematic integration of the large dataset and results from retrospective impact evaluations with prospective mathematical models, developing more reliable forecast scenarios than models which use parameters from other studies or populations. The 18 year-100 million individual retrospective cohort will be used to generate projections, using microsimulation models, of an integrated synthetic cohort up to 2030, maintaining the correlation structure between variables and area/individual-specific trends in all demographic and socioeconomic variables. In creating these forecast cohorts, several alternative scenarios–including maintenance of the current poverty and inequality increase vs their gradual decrease—will be simulated, and resulting effects on mental health-related hospitalizations and suicide (as well as the policy response to it) will be evaluated.

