## Materials and methods

### Conceptual framework

There is a strong association between poverty and poor mental health in young people [17, 18]. Psychiatric disorders in youth are often associated with social problems such as school failure or delinquency, which increase the risk of poverty and other adverse outcomes into adulthood [3, 5]. Furthermore, mental health support is inequitably distributed, so that people living in poverty and those facing other vulnerabilities are at higher risk [5]. Therefore, youth living in LMICs have increased vulnerability to mental illness and associated high mortality rates due to their social and environmental situations [11, 19].

Economic hardship can affect mental health, increase stress, and decrease self-esteem [20]. Economic stressors have been estimated to account for 24% of suicide occurrence [21]. Income inequality is associated with increased suicide rates for both men and women, mechanisms by which this association exists include limited access to resources and increased sense of injustice for not achieving as much economic success as other people [21]. Some studies indicate that poverty is more frustrating in more unequal communities, possibly because individuals become frustrated when comparing themselves to others [22]. In Brazil, income inequality has been associated with higher suicide rates [8] Poverty can increase predisposition to mental illness such as alcohol abuse/dependence and depression in families [22]. It has been shown that cash transfer programs can improve general mental health [23] and increase hope and optimism [24]. It can also reduce factors that are associated with suicide, such as exposure to violence and impulsivity. Factors that can be tested in the current project by accessing notifications and hospitalizations related to those causes.

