**Fig 2 pone.0272481.g002:**
[figure not shown]
Flowchart of non-beneficiary (non-BFP) and beneficiary of the Bolsa Familia Program (BFP) to test the association between BFP and youth mental health-related hospitalizations and suicide.

**Table 1 pone.0272481.t001:** Summary of the dataset’s description, from 2001 to 2018.

Dataset	Description	Sample	Variables of interest
The 100 Million Brazilian Cohort Baseline^70,73^	It was built from socioeconomic and demographic information of individuals applying for social benefits in Cadastro Unico (CadÚnico). CadÚnico is an extensive questionnaire with information on the household and on each individual.	114 million Brazilian cohort, including 66,079,181 Bolsa Familia Program beneficiaries and 47,928,524 non-beneficiaries. Among them 41,764,126, youth aged from 5–24 years old in the day of registration.	Demographic and socioeconomic variables (sex, age, ethnicity, education, work), conditions of the household (type of residence, material of household, household density, household supply, garbage destination etc), Health Care utilization, Institutional and community support (participation in groups, access to Social Assistance Reference Center, etc.) and Brazilian government social protection programs (BFP, etc).
Mortality Information System (SIM)^74,75,72^	The national system aimed to collect information on all deaths in Brazil death certificates. All deaths are recorded using a national standardized form and causes of death are registered according to the updated International Classification of Diseases CID-10.	All mortality cause (n = 21,313,290), including suicide (n = 181,527).	Demographic and socioeconomic variables (sex, age, ethnicity, education, work), place the death took place and primary and secondaries causes of death.
Hospital Information System (SIHSUS)^1^	All hospitalizations admissions financed by the Brazilian National Health System are recorded in this system. It includes about 80% of the Brazilian populations, approximately 150 million people	Hospitalizations from mental illness 5,478,980, including: 1,698,663 from alcohol and substance use-related disorders; 1,952,605 from schizophrenia; 832,974 due mood disorders, etc.	Identification and qualification of the patient, procedures, examinations, and medical acts performed, diagnosis, reasons for discharge, amounts due etc.

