**Aim 2: To test four mechanisms and pathways of the social-economic intervention on reducing mental illness among youth; and Aim 3: To evaluate whether equity was a moderator of the effectiveness of the cash transfer program**, **e.g., whether the Brazilian cash transfer program improved the lives of most vulnerable subgroups (with lower income, black population, and women) compared to less vulnerable groups reducing mental health disparities.**

We will evaluate whether BFP program affects youth mental health through improving social drivers by running Regression Discontinuity Design (RDD) and Propensity Score Matching (PSM), and Structural Equation Modelling (SEM) for each of them and the outcomes. Such strategies allow us to examine the pathways by testing the impact of the intervention on variables that might be on the pathway of the relation between BFP and mental health outcomes. We hypothesize that BFP has an effect on reducing mental health-related hospitalizations and suicide among youth because it also affects their social drivers. Stratified analyses by municipality size, regions, states, and levels of Human Development Index (HDI) will also be performed.

We will include a set of covariates recognized as social drivers of mental illness for youth at the individual level such as income, income instability, unemployment, isolation and at the contextual level, variables from the municipalities where the youth live, such as population, fertility, mortality, migration, housing characteristics, characteristics of the neighbourhood, municipal income, labour, economic inequality (Gini index), Human Development Index (HDI), proportion of poor people and municipal coverage of the community mental health center and number of mental health professionals in the same municipality. We will also evaluate whether equity was a moderator of the effectiveness of the cash transfer program, e.g., whether the Brazilian cash transfer program improved the lives of most vulnerable subgroups compared to less vulnerable groups, thereby reducing mental health disparities. Therefore, we will repeat the analysis stratifying by subgroups with diverse ranges of income level, black compared with the white population, and female compared to male.

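### Aim 3 infers a smaller disparity from a stronger BFP effect in vulnerable groups, an inference that can fail depending on each group's baseline rate, its BFP coverage and the scale

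*Protocol article*

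**What the plan says.** The step from effect to disparity appears in four places in the protocol article.

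- Background, third aim: the program is to be examined for whether it helps vulnerable subgroups "compared to less vulnerable groups, thereby reducing mental health disparities".
- Study innovation, fourth point: the article will assess benefit in the "most vulnerable subgroups (with lower income, black population, and women) compared to less vulnerable groups, therefore, reducing inequalities".
- Conceptual framework, text after Fig 1: "If the effect of the cash transfer is stronger among minorities, decreasing inequalities", this may itself be one of the mechanisms of benefit.
- Analytic strategy, Aims 2 and 3: the question is whether BFP "improved the lives of most vulnerable subgroups compared to less vulnerable groups, thereby reducing mental health disparities".

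The analysis that follows in Aims 2 and 3 is to repeat the effect models, "stratifying by subgroups with diverse ranges of income level, black compared with the white population, and female compared to male". It names no comparison of the gap between groups with and without BFP, and no scale for such a gap. On baseline risk, the Conceptual framework says that "people living in poverty and those facing other vulnerabilities are at higher risk". On coverage, Table 1 gives only the total: the cohort is described as "including 66,079,181 Bolsa Familia Program beneficiaries and 47,928,524 non-beneficiaries".

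**The concern.** Effect modification and change in disparity are different quantities. The first compares the BFP effect across strata. The second compares the distance between two groups' outcome rates with and without the program, and it depends on three things in each group: the rate without BFP, the share receiving BFP, and the effect in recipients. The planned stratified analysis supplies only the third.

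The same groups ("with lower income, black population, and women") are named as vulnerable without distinction by outcome, while Aim 1 lists nine outcomes, from mood disorders to injuries and suicide. If a labelled group has the lower rate for one of them, a stronger effect in that group can push the rates further apart. Aim 3 could then be reported as showing a narrower gap when the gap had widened. A perfectly estimated interaction would not prevent this, because the problem lies in the inference drawn from the estimates.

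**Working it through.** **Inputs from the article.** Beneficiaries 66,079,181 and non-beneficiaries 47,928,524 (Table 1). They sum to 114,007,705, the stated cohort size, so overall coverage is 66,079,181 / 114,007,705 = 0.580. The article gives no rate, effect or coverage by sex, race or income and no disparity figure to reproduce.

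**Assumptions.** All rates (per 100,000), rate ratios and subgroup coverages below are illustrative. Within a group, recipients and non-recipients are taken to share the same rate without BFP.

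**Formulas.** Let v be the labelled group and n the comparator, r the rate without BFP, c the coverage and RR the BFP rate ratio in recipients. A stronger effect in v means RR_v < RR_n.

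- Rate with BFP = r × [1 − c(1 − RR)].
- The ratio v:n falls if and only if c_v(1 − RR_v) > c_n(1 − RR_n).
- The signed difference v − n falls if and only if r_v·c_v(1 − RR_v) > r_n·c_n(1 − RR_n).

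**Equal coverage 0.580, RR_v 0.70, RR_n 0.85.** The multipliers are 1 − 0.580 × 0.30 = 0.826 for v and 1 − 0.580 × 0.15 = 0.913 for n.

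| Rates without BFP (v, n) | Rates with BFP | Absolute gap | Ratio v:n |
|---|---|---|---|
| 12, 8 | 9.91, 7.30 | 4.00 to 2.61 | 1.50 to 1.36 |
| 6, 8 | 4.96, 7.30 | 2.00 to 2.35 | 0.75 to 0.68 |
| 4, 8 | 3.30, 7.30 | 4.00 to 4.00 | 0.50 to 0.45 |
| 2, 8 | 1.65, 7.30 | 6.00 to 5.65 | 0.25 to 0.23 |

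*Labelled group higher (first row).* The inference holds on both scales. With equal coverage this is general: r_v > r_n and RR_v < RR_n satisfy both conditions. A grid of 1,674 assumed combinations (r_v 8.5 to 23.5 against 8, RR 0.50 to 1.00) gave no widening of the signed gap on either scale.

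*Labelled group lower (other rows).* The ratio always moves further from 1. The absolute gap widens only if r_v/r_n > (1 − RR_n)/(1 − RR_v), here 0.15/0.30 = 0.50. So 6 v 8 (0.75) widens, 4 v 8 (0.50) is unchanged and 2 v 8 (0.25) narrows. Over 756 assumed combinations (r_v 1 to 7.5 against 8, same RR range) the ratio widened in 100% and the absolute gap in 60%. The 60% depends on the grid chosen.

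**Unequal coverage, rates 12 v 8, same RRs, c_n 0.580.**

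| c_v | Rate in v with BFP | Gap (from 4.00) | Ratio (from 1.50) |
|---|---|---|---|
| 0.40 | 10.56 | 3.26 | 1.446 |
| 0.30 | 10.92 | 3.62 | 1.495 |
| 0.20 | 11.28 | 3.98 | 1.544 |

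Reversal on the ratio scale needs c_v/c_n < 0.15/0.30 = 0.50. On the difference scale it needs c_v/c_n < (8 × 0.15)/(12 × 0.30) = 0.33.

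**Scale alone.** If effects are measured as risk differences, rates of 12 v 4 with reductions of 2 v 1 become 10 v 3. The gap falls from 8 to 7 while the ratio rises from 3.00 to 3.33.

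**The case against.** The strongest reply is that the article sets no decision rule. The Conceptual framework sentence is conditional, Aim 3 is put as a question, and the planned stratification is neutral. This stands: the text contains a stated inference, not a rule for reporting. But the inference is made four times, and stratified effects are the only analysis attached to it.

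Second, the article's premise is that vulnerable people are at higher risk, and with a higher rate and equal coverage the inference is correct. This also stands, as far as it goes. The premise is general, and the article does not show it for each labelled group and each of the nine outcomes. A reader might infer that some labelled group, such as women for suicide, does have the lower rate and that Aim 3 will therefore be wrong. The article gives no rate by sex, race or income, so it does not support that.

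Third, a reader might take it that a lower rate widens the gap on every scale, or that lower coverage overturns the result. Neither is true in general: the 2 v 8 case narrows the absolute gap, and coverage must fall far short before anything reverses. For income, eligibility for BFP is stricter than for the register (Data and measures), which points to higher coverage among the poorest.

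Fourth, the choice of scale and intervals could be left to a fuller analysis plan. That is fair for such details. It does not cover the stated inference that a stronger effect amounts to a smaller disparity.

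Finally, the microsimulation in Aim 4 is said to suit subgroup impacts, but it compares BFP coverage scenarios for 2019–2030 and names no between-group gap. It does not fill the hole.

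**Conclusion.** The concern holds in a limited form. A stronger BFP effect in a labelled group does not by itself show that a disparity has shrunk, and Aim 3 as described estimates nothing else that would show it. The inference is sound for relative effects when the labelled group has the higher rate and coverage is equal. With a lower rate and equal coverage it always fails on the ratio scale, and it fails on the absolute scale when the labelled group's rate reduction is the larger one. In the 6 v 8 example the gap widens by 0.35 per 100,000 (2.00 to 2.35) and the ratio moves from 0.75 to 0.68. Lower coverage is the weaker route to failure: for rate ratios of 0.70 v 0.85, it must be below half the comparator's to reverse the ratio.

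Apart from the overall 58% coverage, every figure here is assumed. Whether any of the income, race or sex contrasts meets a failure condition cannot be told from the article. The point is that the plan does not check, on the question Aim 3 asks.

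**What to change.** In Aim 3, for each outcome and each income, race and sex contrast:

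- Estimate the between-group rate difference and rate ratio twice, as observed and as estimated without BFP, over the whole group (recipients and non-recipients), from each group's rate, coverage and effect, with intervals.
- Base the disparity conclusion on the change in the gap on both scales, and say so where the two disagree.
- Identify the worse-off group for each outcome from its estimated rate without BFP, not from the prior label.

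Reword the third aim in Background, the fourth point of Study innovation, the equity sentence in the Conceptual framework and the Aim 3 text, so that a stronger stratum effect is reported as effect modification and not as reduced disparity.

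The cohort already holds recipients and non-recipients with linked outcomes, so the cost is rewording and a little post-estimation from models already planned. The downside is that some outcomes may show no disparity for BFP to reduce, or give different answers on the two scales.

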#### Data and measures

Datasets, variables, and sample sizes.

***100 Million Brazilian Cohort*.** We will analyze a cohort of subjects registered in Unified Registry for Social Programs (CadÚnico). The CadÚnico is a data collection and storage system that contains individual records with demographic and socioeconomic information on the poorer half of the Brazilian population (n = 114,007,705). Anyone who meets the eligibility criteria can be registered by visiting one of the Centers for Social Assistance (CRAS) or be registered at home, as social workers visit households periodically to identify and register eligible individuals. The criteria to be eligible for CadÚnico registration are: having a monthly family income per capita of half the minimum salary in Brazil (778 reals in 2015) or less; or having a total family income (monthly) of up to three minimum salaries. The CadÚnico contains information about housing conditions, income and demographic characteristics of all the members of a registered family [26].

***Bolsa Familia Program (BFP)*.** The Brazilian Cash Transfer Program (BFP) is the largest poverty alleviation program in the world, with about 46 million people having received the benefit up to 2015. It has three aims: income supplement guarantee for immediate relief of extreme poverty (people who live with up to 70 reals per capita) [27]; access to public services (improving education, health, and citizenship of families); and productive inclusion to increase the capacity and job opportunities, and income generation among the poorest families [28].

In 2014, the eligibility criteria for participation in the program (which is more stringent than the conditions for eligibility to register in CadÚnico) was having an income of less than 77 reals (14 USD) monthly per person or less than 154 reals in cases where there is a child, adolescent or pregnant woman in the family. The benefits were: “basic benefit”, 77 reals monthly, regardless of family composition; an extra 35 reals to families with a child or adolescent between 0–15 years, or a pregnant or nursing woman; and an extra 42 reals per adolescent from 16–17 years, in 2014. Families living in extreme poverty can accumulate all these “basic benefits” to a maximum of 1,332 reals per month (235 USD).

All BFP beneficiaries are registered in an electronic register called CadÚnico (Unified Registry for Social Programs). Since we have both datasets available, we hold information from people who are beneficiaries in the programs and also from people who are not (see Table 1 & Fig 2) and we will be able to compare them by using robust methodologies further discussed below. A strength of the use, of a 114 million cohort, is that it covers a major part of the poor Brazilian population registered on the CadÚnico. It is especially important when we are evaluating a socioeconomic policy, and these are the people for whom the cash transfer can potentially affect the most. As we have information from all causes of death, our follow-up is more precise than other studies that cannot censor those events.

